### Interventions

2.4

Individuals who meet the eligibility criteria will be randomized (1:1:1) to receive either 0.5 mg M-001 (low dose), 1.0 mg M-001 (high dose), or saline (placebo control). All subjects will receive 2 i.m. administrations of the test vaccine, or saline, followed by 1 i.m. administration of an investigational (whole virus, inactivated, AlPO_4_-adjuvanted) prepandemic influenza vaccine (H5N1) produced by Fluart Innovative Vaccines Ltd (formerly Omninvest Ltd). The prepandemic vaccine contains 3 μg HA, which is half of the dose of the pandemic vaccine licensed in Hungary.

### Outcomes

2.5

#### Primary outcomes

2.5.1

The trial has 2 primary outcomes. The first primary outcome is the cellular immune response elicited by M-001, evaluated by multiparametric flow cytometry analysis in all subjects on days 0 and 42. Multiparametric flow cytometry will be performed after 24 h in vitro stimulation of PBMC with vaccine antigen. Markers including clusters of differentiation 3 (CD-3), CD-4, and CD-8 will be used to define cell lineage, and interferon gamma (IFN-γ), interleukin (IL)-2, IL-4, and tumor necrosis factor alpha (TNFα) will be used to detect specific cytokine responses. The other primary outcome is safety evaluation. This includes the solicited AEs in all subjects until 21 days after the last dosing of the study vaccine and the unsolicited AEs and SAEs in all subjects for 180 days after the first injection. The investigator will assess the intensity of the AE and the relationship between the tested vaccine and the occurrence of the AE (Table 2).

**Table 2 T2:**
[figure not shown]
Adverse events’ classification.

#### Secondary outcomes

2.5.2

The secondary outcome is serum hemagglutination inhibition (HAI) titers specific for the H5N1 study vaccine strain (A/Vietnam/1194/2004) in all subjects on days 0 and 63 (21 days following the H5N1 vaccination). HAI tests will be performed by standard procedures with chicken red blood cells and 4 HA units of virus/well.^[23]^

#### Exploratory outcomes

2.5.3

The following exploratory outcomes are considered; (1) cellular immune response elicited by M-001, with or without prepandemic H5N1 vaccine, evaluated by quantitative reverse transcription polymerase chain reaction (qRT-PCR) of cytokine mRNA on days 0, 42, and 63 in a subset of 60 subjects; (2) serum HAI titers toward H5 drifted strains evaluated on days 0 and 63 in all subjects; (3) serum single radial hemolysis (SRH) titers evaluated on days 0 and 63 in all subjects toward the H5N1 vaccine strain; and the association between the CMI markers analyzed and (4) the HAI responses.

### Sample size calculation

2.6

Though a variety of immune parameters will be analyzed during the trial, the minimum sample size is determined on the basis of the expression of IFN-γ producing CD-8+ cells, as this T-cell subset is important for influenza viral clearance.^[24,25]^ We estimated a background rate of 5% in the placebo group and it is expected that the M-001 vaccine will result in at least 5 times higher rates, or an absolute rate of 25% responders in the vaccinated arms.^[21]^ To be able to detect this with a power of 80%, approximately 60 subjects per arm are needed based on a 2-group continuity corrected test with a 0.05 two-sided significance level. Taking 15% loss of follow-up into account, a total of 222 subjects (74 subjects per treatment group) is required. It should be noted that estimates are based on data analysis from a previous trial where multiparametric flow cytometry analysis was performed on only a small sample size of 10 elderly participants.

### Randomization

2.7

Eligible subjects will be randomized 1:1:1 to 1 of the 3 treatment groups. Within each treatment group block randomization will be done for participants aged <50 years and ≥50 years to achieve an approximately balanced age distribution.^[26]^ Randomized subjects will be allocated the next sequential 3-digit randomization number available at the trial site which is identical to the treatment number allocated by the randomization list.

### Blinding

2.8

The study will be double-blinded. To maintain blinding, the preparation of the M-001 formulations and control will be performed by an unblinded qualified person (QP) other than the person giving the injection. The reason for this is that M-001 and saline differ in appearance. The unblinded QP will prepare the dosing solutions and will use the study randomization code to assign each subject to the appropriate treatment group. The unblinded QP will not reveal the treatment code to other study personnel or perform any other study treatment-related activities. The unblinded QP will prepare syringes containing the study medication assigned by the randomization scheme. The syringe content will be hidden by a label, which includes the subject's randomization number, initials, and date of birth. An identical label will be attached to the top of the case report form. This material will be given to the blinded study personnel administering the injections. The pharmacy file, including the randomization list, vaccine supplies, and all associated documentation, will be stored in a locked cabinet within the pharmacy to which only the unblinded pharmacy personnel have access.

### Statistical analysis and report

2.9

A statistical analysis plan (SAP) will be developed according to the Consolidated Standards of Reporting Trials 2010 guidelines before the database lock.^[27]^ Both intention-to-treat (ITT) and perprotocol analysis will be performed for the analyses of reported AEs and SAEs, the measured serum HAI titers, SRH titers, and the cellular immune response measured by both multiparametric flow cytometry and qRT-PCR assays. ITT analysis will include all vaccinated subjects who receive the first vaccination. Perprotocol analysis will include the subjects who complete the assigned schedule of vaccination, who meet the inclusion and exclusion criteria, and who comply with the procedures defined in the protocol (i.e., vaccinated according to their randomized assignment, not vaccinated with any vaccine or treated with any medication not foreseen or forbidden in the protocol, free of underlying medical conditions forbidden by the protocol) until the days of assessment and have not broken the randomization code. Both analyses will be conducted to assess differences from baseline with their corresponding 95% CIs. Differences in continuous variables will be tested using the analysis of variance (ANOVA)/T-tests or distribution-free tests. In addition, subgroup analyses are preplanned according to age (<50 and ≥50 years) and ANOVA or Kruskal–Wallis test will be applied to test for potential differences between the treatment groups. All calculations will be performed using SAS for Windows. The measured variables and derived parameters will be listed individually by subject number and treatment group. The data will be summarized in appropriate tables presenting sample size, arithmetic mean, standard deviation, minimum, median, and maximum values by treatment group for continuous data and absolute and relative frequency by treatment group for categorical data.

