### Study design

2.1

The study is a multicenter, randomized, double-blind, and controlled phase IIb trial involving 222 healthy volunteers aged 18 to 60 years over a period of 187 days (from screening to study conclusion). Individuals volunteering to participate in the study will be screened before enrollment in the trial. Subject eligibility will be assessed during the screening and written consent will be obtained (Fig. 1). The eligible subjects will be randomized to receive 2 administrations of M-001 at low or high dose, or saline as placebo. All participants will receive an investigational AlPO_4_-adjuvanted, inactivated whole virus prepandemic H5N1 vaccine as a third administration to evaluate whether M-001 has a priming effect. The H5N1 vaccine is based on a clade 1 virus A/Vietnam/1194/04. Each administration will be given intramuscularly (i.m.) 21 ± 2 days apart. Blood samples will be taken from all subjects on days 0 (before the first vaccination), 42 (21 days after the second vaccination), and 63 (21 days after the H5N1 vaccination) for serum and peripheral blood mononuclear cells (PBMCs) to evaluate the influenza-specific cellular and humoral immune responses. Additionally, questionnaires/diaries concerning AEs will be issued on days 0 and 21 to subjects for the collection of solicited (e.g., fever, chills, joint pain, muscle pain, sore throat, fatigue, injection site reactions) and unsolicited AEs. The cards will need to be completed by the subjects and returned on day 21 (second vaccination of study vaccine) and day 42 (H5N1 vaccination). Unsolicited AEs and SAEs will be followed throughout the whole study period and thereby AEs from both the study vaccine and H5N1 vaccine. The study will be conducted at the St. Istvan and St. Laszlo Hospital of Budapest (Hungary) and another Hungarian satellite trial site (Béke Hospital, Budapest).

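### Section 2.9 frames the main analyses as change from baseline and does not carry over the M-001 versus placebo comparison on which the trial is sized

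*Protocol article*

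**What the plan says.** All of the analysis wording at issue is in section 2.9 (Statistical analysis and report) of the protocol article.

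- Target of the ITT and per-protocol analyses: "Both analyses will be conducted to assess differences from baseline with their corresponding 95% CIs". No comparator arm is named.
- Tests: "Differences in continuous variables will be tested using the analysis of variance (ANOVA)/T-tests or distribution-free tests". The sentence does not say which groups or time points are compared, and it names no covariate.
- Between-group testing: a sentence that opens "In addition, subgroup analyses are preplanned according to age (<50 and ≥50 years" continues "ANOVA or Kruskal–Wallis test will be applied to test for potential differences between the treatment groups". With three arms this is a global test.
- Categorical data: absolute and relative frequencies by group. No test is named.

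Other sections describe a comparison between arms.

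- Section 2.6 (Sample size calculation): "We estimated a background rate of 5% in the placebo group", against "an absolute rate of 25% responders in the vaccinated arms", using a two-group continuity-corrected test at two-sided 0.05.
- Section 2.1 (Study design): every participant receives the "prepandemic H5N1 vaccine as a third administration to evaluate whether M-001 has a priming effect".
- The Discussion says that HAI titres after the H5 vaccine will be assessed with and without M-001 priming.

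**The concern.** The trial asks two questions: does M-001 raise the cellular response, and does it prime for H5N1? In a placebo-controlled randomised trial, the contrast with placebo answers both. Section 2.9 attaches its confidence intervals to change from baseline and leaves that contrast unstated.

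Three things follow.

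1. The comparison that justifies 222 subjects, a responder proportion, has no counterpart in the analysis section.
2. For HAI, a before-after interval within an arm mixes the response to H5N1 with any priming effect.
3. A global ANOVA or Kruskal–Wallis test does not say which dose differs from placebo. Change scores also use the day-0 value less efficiently than adjusting for it does.

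**Working it through.** **1. The plan's own sizing figure.** Inputs from section 2.6: p1 = 0.05, p2 = 0.25, two-sided alpha 0.05, power 80%, continuity correction. The mean proportion is 0.15 and the difference d = 0.20.

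- Uncorrected: n = [1.96·√(2·0.15·0.85) + 0.8416·√(0.05·0.95 + 0.25·0.75)]² / 0.20² = (0.990 + 0.408)² / 0.04 = 48.8, so 49 per arm.
- Corrected: (48.8/4)·[1 + √(1 + 4/(48.8·0.20))]² = 58.4, so 59 per arm. The article says approximately 60, so the figure reproduces.
- After 15% loss: 60/0.85 = 70.6, so 71 per arm or 213 in total. The stated 74 per arm leaves 74 × 0.85 = 62.9 evaluable, slightly on the safe side.
- Continuity-corrected power at alpha 0.05 is 81% with 60 per arm and 83% with 63.

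The sized comparison is therefore one M-001 arm against placebo on a proportion.

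**2. Sizing and analysis side by side.**

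| | Section 2.6 | Section 2.9 |
|---|---|---|
| Comparison | M-001 arm vs placebo | change from baseline; arms named only in the age-subgroup sentence |
| Endpoint type | responder proportion | tests for continuous variables; frequencies only for categorical data |
| Test | two-group, continuity corrected | ANOVA/t-tests or distribution-free; ANOVA or Kruskal–Wallis over groups |

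**3. What a within-arm change can show.** Let h be the mean log2 HAI change from day 0 to day 63 due to the H5N1 injection, and p the extra change due to priming.

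- Placebo arm: h.
- M-001 arm: h + p.
- Difference between arms: (h + p) − h = p.

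A before-after interval in an M-001 arm estimates h + p. It can exclude zero when p = 0, because h alone may be positive. Only the difference between arms isolates p.

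The primary cellular outcome is different. It is "evaluated by multiparametric flow cytometry analysis in all subjects on days 0 and 42". With injections 21 days apart, H5N1 is given on day 42 and its own follow-up sample is day 63. By day 42 the placebo arm has had saline only, so H5N1 contributes no common rise to this outcome.

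**4. Precision for continuous endpoints.** Assume equal variance σ² at day 0 and follow-up, with correlation r. The article does not give r.

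- Variance per subject, change score: 2σ²(1 − r).
- Variance per subject, ANCOVA: σ²(1 − r²).
- Ratio: (1 − r²) / [2(1 − r)] = (1 + r)/2.

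The detectable difference with 60 per arm and 80% power is 2.8016·√(2V/60), in SDs of the follow-up value, where V is the variance above divided by σ².

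| r (assumed) | Variance ratio | Change score | ANCOVA |
|---|---|---|---|
| 0.3 | 0.65 | 0.61 SD | 0.49 SD |
| 0.5 | 0.75 | 0.51 SD | 0.44 SD |
| 0.7 | 0.85 | 0.40 SD | 0.37 SD |
| 0.8 | 0.90 | 0.32 SD | 0.31 SD |

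These figures do not transfer to the responder proportion, which is the endpoint that was powered.

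**The case against.** The strongest reply is that the plan already intends a placebo comparison. Section 2.6 names one, the Discussion contrasts primed with unprimed subjects, and the design is randomised with a placebo arm. In a three-arm trial, ANOVA on change from baseline most naturally compares the arms, and t-tests can serve as the pairwise comparisons. Change from baseline may simply be the outcome variable. The second half of the age-subgroup sentence may apply to the whole sample. A between-arm comparison of change scores is unbiased under randomisation, so a missing covariate is not an error, and an article may leave model details to the SAP that it promises.

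Most of this stands. It rules out two stronger readings that a reader might draw. One is that the article nowhere provides for a comparison between arms; section 2.6 and the Discussion contradict that. The other is that the trial would be judged on before-after intervals, so that a rise in an M-001 arm without one in placebo would count as an effect. The wording allows that reading but does not commit to it. Any false-positive rate attached to it would need an assumed common rise and SD that the article does not give.

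The objection does not remove the gap. Section 2.9 is not silent: it states a target, and that target does not match the comparison used for sizing. For HAI, the reading that section 2.9 leaves open cannot answer the priming question.

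**Conclusion.** The point holds as a matter of alignment and of a better analysis available at no cost in data. Section 2.9 states change from baseline as the target, leaves it unclear whether the arms are compared outside the age subgroups, and gives no test for the responder comparison that sized the trial. Within-arm HAI change cannot show priming. This is a matter of design and needs no assumed figures, but it concerns the secondary outcome and not the primary day-42 cellular response.

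The precision gain is conditional. The variance is 0.65 to 0.85 of that of change scores if r lies between 0.3 and 0.7 and the variances are equal at both times, and the gain shrinks as r rises. The missing covariate costs precision and introduces no bias. No error in the sample size follows from this point: 59 per arm agrees with the stated figure.

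**What to change.** State in section 2.9 terms, and in the SAP before database lock, that the effect measure is each M-001 dose versus placebo in the ITT set, with 95% CIs:

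- **Day-42 cellular response, responder proportion** (the sized comparison): each dose versus placebo, stratified by age group (<50, ≥50 years).
- **Day-42 cellular response, continuous, log scale:** ANCOVA on arm, day-0 value and randomisation age stratum.
- **Day-63 HAI, log2 scale:** the same model with the day-0 titre.
- **Within-arm change:** keep as description.
- **Global test:** replace with the two dose-versus-placebo contrasts.

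The cost is wording. Day-0 values are already collected in all subjects, and the age stratum is already used in randomisation. The sample size does not change if each contrast is tested at two-sided 0.05, as in section 2.6. The SAP should say whether alpha is shared between the two doses: at 0.025 each, the same formula gives 69 per arm, and power with 63 evaluable per arm is 75%.

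### Allocation is blocked by age, but the named tests carry no age-stratum term, and the preplanned age subgroups have between-arm tests without a treatment-by-age interaction

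*Protocol article*

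**What the plan says.** Section 2.7 of the protocol article sets the allocation: "Eligible subjects will be randomized 1:1:1 to 1 of the 3 treatment groups". It then makes age a blocking factor: "Within each treatment group block randomization will be done for participants aged <50 years and ≥50 years", with the stated aim of balancing age.

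Section 2.9 names the tests: "Differences in continuous variables will be tested using the analysis of variance (ANOVA)/T-tests or distribution-free tests". No age factor is attached to them. The next sentence preplans the age analysis ("subgroup analyses are preplanned according to age (<50 and ≥50 years") and continues: "ANOVA or Kruskal–Wallis test will be applied to test for potential differences between the treatment groups". No treatment-by-age interaction is named.

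Section 2.9 also leaves detail to a later document: "A statistical analysis plan (SAP) will be developed according to the Consolidated Standards of Reporting Trials 2010 guidelines before the database lock".

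**The concern.** Two ordinary principles are involved.

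- **Analyse as randomised.** Blocking within age strata removes chance age imbalance between arms. An analysis that ignores the strata still counts the age-related variance as noise, so its standard errors are too large whenever age predicts the outcome. A t-test and a Kruskal–Wallis test cannot carry a stratum term. ANOVA can, but none is named.
- **Test the difference, not the pair of p-values.** A between-arm test within each age group asks whether there is an effect in that group. It does not ask whether the effect differs by age. One significant and one non-significant result is a common outcome when the effects are equal, because each group is smaller than the whole trial.

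At stake are some precision in the between-arm comparisons and the soundness of any later statement about age. The primary comparison is not at risk of a false positive from either point.

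**Working it through.** **1. The plan's own figure.** Section 2.6 gives 5% against 25% responders ("We estimated a background rate of 5% in the placebo group"), 80% power, two-sided 0.05, continuity corrected.

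- Uncorrected: n = [1.96·√(2·0.15·0.85) + 0.8416·√(0.05·0.95 + 0.25·0.75)]² / 0.20² = (0.990 + 0.408)² / 0.04 = 48.8.
- Corrected: (48.8/4)·[1 + √(1 + 4/(48.8·0.20))]² = 58.4, so 59 per arm. The stated figure of about 60 reproduces.
- Loss of 15%: 60/0.85 = 70.6, so 71 per arm and 213 in total. The stated 74 per arm (222) is slightly larger, on the safe side.
- Evaluable per arm: 74 × 0.85 = 62.9, taken as 63 below.

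The sample size does not depend on the present point.

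**2. Leaving out the stratum (continuous readouts).** The article gives neither the share aged 50 or over (f) nor the age effect in within-stratum SDs (D). Both are assumptions. With balanced strata:

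- ratio of unadjusted to correct SE: r = √(1 + f(1−f)D²)
- type I error of a two-arm unadjusted test: 2·[1 − Φ(1.96·r)]

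The last column is a simulation of the three-arm ANOVA without the stratum (normal outcomes, 63 per arm, 20,000 trials per setting).

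| f | D | SE ratio r | Type I error, formula | Type I error, simulated |
|---|---|---|---|---|
| 0.5 | 0 | 1.000 | 0.050 | 0.050 |
| 0.5 | 0.2 | 1.005 | 0.049 | not run |
| 0.5 | 0.5 | 1.031 | 0.043 | 0.041 |
| 0.5 | 1.0 | 1.118 | 0.028 | 0.024 |
| 0.3 | 0.5 | 1.026 | 0.044 | 0.044 |
| 0.3 | 1.0 | 1.100 | 0.031 | 0.025 |

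With the stratum in the model, simulated type I error is 0.049–0.052. For a 0.5 SD effect in both M-001 arms, power is about 0.83 adjusted. Unadjusted, it is 0.81 at D = 0.5 and 0.74–0.75 at D = 1.0.

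**3. Limit for the responder endpoint.** Age can explain only so much of a 5% response rate. With f = 0.3 and all responders in the older group, their rate is 0.05/0.3 = 0.167. Then R² = 0.3·0.7·0.167²/(0.05·0.95) = 0.12, and the SE is at most 1/√(1 − 0.12) = 1.07 times too large. If all responders are younger, R² is at most about 0.02. The upper end of the table therefore belongs to continuous readouts.

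**4. Separate tests in each age group.** Assume the true effect is 5% against 25% in both groups, with 63 evaluable per arm. For one M-001 arm against placebo with n per arm in a stratum, uncorrected power is Φ{[0.20 − 1.96·√(0.255/n)]/√(0.235/n)}. The continuity-corrected version subtracts 1/n from 0.20. With powers a and b, the chance that exactly one group is significant is a(1−b) + b(1−a).

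| Share ≥50 | n per arm, <50 / ≥50 | Power, uncorrected | Exactly one | Power, corrected | Exactly one |
|---|---|---|---|---|---|
| 50% | 32 / 31 | 0.615 / 0.601 | 0.48 | 0.471 / 0.454 | 0.50 |
| 30% | 44 / 19 | 0.756 / 0.404 | 0.55 | 0.650 / 0.237 | 0.58 |
| 20% | 50 / 13 | 0.809 / 0.290 | 0.63 | 0.720 / 0.130 | 0.66 |

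For example, at 30%: 0.756·0.596 + 0.404·0.244 = 0.55. The normal approximation is rough in the smallest cells. The three-arm simulation with a normal outcome agrees: about 0.50 at f = 0.5 and 0.56 at f = 0.3. In the same simulation the treatment-by-age interaction test was falsely significant in 4.8–5.2% of trials.

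With no effect in either group, at least one subgroup test is significant in 1 − 0.95² = 9.75% of trials, and exactly one in 2·0.05·0.95 = 9.5%.

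**The case against.** The strongest reply is that this is SAP detail. A condensed article commonly leaves covariates and interaction terms to the SAP, and ANOVA as named can hold both. That stands in part: a missing age covariate would be a weak finding on its own. But the article does name its methods. The t-test and Kruskal–Wallis test cannot hold the stratum, and a between-arm test is attached to the age subgroups in the same sentence that preplans them.

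Three stronger readings are tempting, and the article does not support them.

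- **A spurious age difference is likely.** Section 2.9 does not say outright that tests are run separately in each age group, although that is the natural reading, and a two-way ANOVA is not excluded. Nor does it plan to compare significance between the groups, and none of the outcomes in section 2.5 is an age hypothesis. The 48–66% arises only if a reader makes that comparison.
- **The error bars are invalid.** The error runs one way, towards caution, and only if age predicts the outcome. At D = 0.2 it is about 0.5%. Section 2.9 also looks at differences from baseline, which may already remove some age-related variation.
- **Section 2.7 does not stratify.** Read literally, blocks within a treatment group could not balance arms by age. The stated aim, "block randomization will be done for participants aged <50 years and ≥50 years to achieve an approximately balanced age distribution", shows that ordinary age-stratified blocks are meant. The literal reading would also undo the standard-error argument, because unadjusted tests are correctly sized when allocation is not stratified.

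Nothing here supports adding site to the models: section 2.7 names no site stratification.

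**Conclusion.** The point holds as a no-cost improvement of modest size. The named analyses do not use the age stratum that shaped the allocation, and the age subgroups have no interaction test.

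- Omitting the stratum costs precision only: SEs are 0–12% too wide and type I error is between 0.05 and about 0.025. This rests on an assumed age effect of 0–1 SD in a continuous readout. For the 5% responder rate with 30% aged 50 or over, the SE excess cannot exceed about 7%.
- Separate subgroup tests would disagree in about half of trials or more (48–66%) with identical effects, against about 5% false signals from an interaction test. This rests on 20–50% of subjects being aged 50 or over, 63 evaluable per arm, and the condition that someone compares significance across groups.

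The trial's validity, sample size and false-positive risk for its main comparisons are not in question.

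**What to change.** In section 2.9 and the SAP:

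1. Include the randomisation age stratum as a factor in the between-arm analyses: two-way ANOVA or ANCOVA for continuous readouts, a stratified rank test such as van Elteren where a distribution-free test is used, and Cochran–Mantel–Haenszel for responder rates.
2. Assess age by a treatment-by-age interaction with its 95% CI, and present the subgroup estimates with CIs as descriptive. The interval matters more than the p-value, because an interaction will be imprecisely estimated. With 19 older placebo subjects and a 5% rate, about one responder is expected (19 × 0.05 = 0.95).

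As a minor clarification, reword section 2.7 to say that treatments are allocated in blocks within each age stratum.

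The cost is a few sentences in a SAP that is still to be written before database lock, and one sentence on randomisation. No subjects, visits, samples or sample-size change are needed.
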